## Abstract

**Background:**

People with chronic obstructive pulmonary disease (COPD) sometimes experience anxiety, depression and comorbid cognitive deficits. Rather than being merely a consequence of symptom-related physical impairments these additional problems may be part of the clinical course of the condition. The relationship between the physical and psychological aspects of the condition is illustrated by the patterns of use of non-invasive ventilation (NIV); NIV is often rejected or used inappropriately, resulting in clinical deterioration and an increase in health care costs.

The study aims to analyse the effects of psychological support on the acceptance of, and adherence to, NIV. The primary outcome will be a latent variable related to indices of use of NIV equipment and adherence to treatment regime; while survival rates and psychological variables will constitute the secondary outcomes.

**Methods:**

A two-arm randomised controlled trial will be conducted. We aim to recruit 150 COPD patients for whom NIV is indicated. The experimental group will receive a brief course of psychological support that will include counselling, relaxation and mindfulness-based exercises. In some cases, it will also include neuropsychological rehabilitation exercises. Support will be delivered via four to eight meetings at the HD Respiratory Rehabilitation Unit, at home or via telemedicine. Controls will receive standard care and watch educational videos related to the management of their disease.

**Discussion:**

This investigation will gain insight about the role of a psychological intervention as part of a treatment plan during the process of adaptation to NIV in COPD patients.

**Trial registration:**

ClinicalTrials.gov, ID: NCT02499653. Registered on 14 July 2015.

**Electronic supplementary material:**

The online version of this article (doi:10.1186/s13063-017-1802-1) contains supplementary material, which is available to authorized users.

## Background

Chronic obstructive pulmonary disease (COPD) is the fourth leading cause of death in the world [1], the seventh cause of disability-adjusted life years (DALYs) and the tenth cause of early death (measured as years of life lost (YLL)) [2]. This clinical condition involves an irreversible obstruction of the airways, associated with progressive and chronic inflammation of the lung tissue; it develops slowly and adversely affects both quality of life (QoL) and psychological wellbeing [3], leading to high levels of anxiety and depression [4, 5]. The latter two are also associated with fatigue, shortness of breath and an increase in symptom exacerbations [6], engendering a psychological vicious circle of negativity [7–9]. Systematic reviews state that the prevalence of depression ranges between 7% and 42% [10], whereas that of anxiety varieties between 10% and 19% [11].

Cognitive deficits, whether global or in specific domains, such as perception, memory, attention [12–14], learning, visuospatial and construction abilities and language skills [15, 16], can also have an impact on functional, social, emotional and communication skills [17]. Moreover, COPD is associated with a significant risk of developing mild cognitive impairment, especially in patients older than 70 years [18].

Preliminary evidence suggests that it is necessary to pay attention to psychological factors in both therapy and rehabilitation [19–21]. Psychological changes may be a consequence of physical symptoms, but they may also influence the course of the disease, as in other chronic conditions [22].

Patterns of acceptance of non-invasive ventilation (NIV) are examples of the interaction of psychological and physical factors. Despite the fact that NIV can produce significant clinical improvement in their condition, patients often reject it or fail to use it appropriately. NIV rejection or its inappropriate use results in worse clinical outcomes and increased health care costs. Appropriate use of NIV is crucial, given that adherence to medication decreases over time and is inversely related to the number of drugs prescribed [23, 24]. Acceptance and adherence to NIV treatment can reduce hospital admissions and physician visits [25]. Using NIV requires the patient to make some behavioural and lifestyle changes, such as changes in daily routine to allocate time for ventilation, and this may reduce adherence to the treatment [24]. Treatment adherence may also be adversely affected by the use of different drugs and devices, or because patients receive inadequate education about the illness and associated morbidities from their physician [26, 27].

Clinical experience suggests that patients with cognitive deficits [12, 28, 29] or psychological problems, such as anxiety and depression, are less likely to accept and comply with NIV regimes; however, there has been little research on this. The few available studies focussed on early NIV failure (defined as the need for endotracheal intubation or death within 24–48 h of starting NIV) [30, 31], quantifying adherence [32] and largely neglected predictors of nonadherence [33]. No study has identified the individual psychological factors that increase the risk of rejection or improper use of NIV. Previous studies suggest that COPD patients who clearly demonstrated a lower survival benefit from the NIV usage exhibit worse average daily NIV adherence, because of the imbalance between the constraints that NIV imposes and the improvement that patients’ perceive in their condition [34]. Ventilator settings are not easy to adjust and they influence sleep quality, which has spill-over effects on daytime life [34, 35]. The effects of psychological support in promoting the machine’s acceptance have also not been adequately investigated.

### Objectives

The primary objective of the study is to evaluate the effects of psychological support on the acceptance of, and adherence to, NIV. Secondary aims include assessment of the change in QoL between baseline and after 3, 6 and 12 months following recruitment, identification of psychological and clinical factors that predict rejection or misuse of NIV, and factors that predict the success of the psychological intervention.

The primary outcome will be a latent variable related to indices of use of NIV equipment and adherence to treatment regime: the effects on change from baseline in acceptance to NIV in COPD patients at 3, 6 and 12 months as measured by weekly means and standard deviations of hours of use of NIV as recorded by the ventilator and changes in adherence defined as the difference between prescribed and effective NIV hours. Change in QoL will also be measured relative to baseline at 3, 6 and 12 months using the EuroQoL (EQ-5D) questionnaire, respiratory, functional and biomedical parameters. Survival rates after starting the adaptation to NIV and psychological variables will be considered as secondary outcomes.

As well as evaluating clinical and psychological variables we will also evaluate econometric outcomes. The study will explore the potential impact of the psychological intervention on the cost to the Italian welfare system of providing health care for patients with COPD. These assessments will be based on standard econometric indices (e.g. quality-adjusted life years (QALYs); DALYs).

Finally, semistructured interviews will be conducted to gain insight into patients’ perceptions of NIV.

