### Proposed analyses

Descriptive analyses will be performed for all study variables. We will assess the effect of the interaction between treatment (experimental versus control) and time (three repeated measures) on primary outcome variables (acceptance of treatment; adherence to treatment). Missing data will be imputed with multiple imputation techniques [58, 59].

Before-after differences will be analysed with appropriate within-group tests (paired samples *t* test; Wilcoxon test). Multiple regression will be used to assess the influence of baseline variables on outcome indicators and identify predictor variables.

The analysis will be performed using the intention-to-treat procedure. The significance level will be 5% (*p* ≤ 0.05). Data analysis will be performed using SPSS software.

Data collection and analysis will begin in month 1 and will last for 24 months, i.e. until 1 month after the last follow-up data have been collected.

We will report reasons for withdrawal for each randomisation group and compare the reasons qualitatively. The effect that any missing data might have on results will be assessed via sensitivity analysis of augmented data sets. Dropouts (essentially, participants who withdraw consent for continued follow-up) will be included in the analysis by modern imputation methods for missing data.

For more details about the trial, refer to the SPIRIT Checklist (Additional file 1).

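### The primary outcome is one latent variable in the Objectives but two named variables in the analysis section, and the sample size fits a single comparison; one primary must be named

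*Protocol article*

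**What the plan says.** The Objectives (and the Abstract) define the primary outcome in the singular: "The primary outcome will be a latent variable related to indices of use of NIV equipment and adherence to treatment regime". They then list its ingredients. Acceptance is described as "the effects on change from baseline in acceptance to NIV in COPD patients at 3, 6 and 12 months", measured by "weekly means and standard deviations of hours of use of NIV as recorded by the ventilator". Adherence enters as "changes in adherence defined as the difference between prescribed and effective NIV hours".

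Proposed analyses describes a treatment-by-time interaction "on primary outcome variables (acceptance of treatment; adherence to treatment", the closing bracket following directly. It mentions no latent variable, composite score or measurement model. It sets one significance level of 5% and gives no rule for combining the two variables.

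The Sample size section gives 128 patients (80% power, t on 126 degrees of freedom) to 172 (90% power, 170 degrees of freedom), with 150 planned. It does not say which variable or visit is being powered.

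On NIV status at entry, the Abstract says "We aim to recruit 150 COPD patients for whom NIV is indicated" and places the trial "during the process of adaptation to NIV in COPD patients". Recruitment and duration describes T0 as a psychological assessment after consent. No baseline period of ventilator recording is defined.

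**The concern.** The primary outcome decides whether the trial has succeeded, and this article leaves it open. A reader of the Objectives expects one test on a latent score. A reader of Proposed analyses expects acceptance and adherence to be analysed as two primary variables. A reader of Sample size expects one two-group comparison. Any analysis plan written underneath has to depart from at least one of these sections. If the choice is made after results are known, the nominal 5% no longer describes the chance of a false positive claim.

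Two of the ingredients make the choice harder. The weekly SD of hours does not rank patients by how well they accept NIV. A change from baseline needs a baseline, and a patient who is only starting NIV has either zero recorded hours or none.

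**Working it through.** **1. The plan's own figures.** Inputs from Sample size: two-sided α = 0.05 (implied by t = 1.97), power 0.80 and 0.90, df 126 and 170. Assumed: 1:1 allocation and standardised difference d = 0.5, back-solved because no effect size is given. For a two-sample t test (noncentral t):

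- power 0.80: 63.8 per arm, rounded up to 64, N = 128; critical t(126) = 1.979
- power 0.90: 85.03 per arm, rounded up to 86, N = 172; critical t(170) = 1.974
- 150 is the midpoint, (128 + 172)/2, and gives 86.0% power at d = 0.5

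The figures reproduce as one comparison of one variable. If α were split as 0.025 for each of two primaries, N = 150 would give 78.7% power per test, and 80% power would need 78 per arm (77.3 rounded up), N = 156.

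**2. Familywise error if either variable alone could win.** For independent tests it is 1 − 0.95² = 9.75%. For correlated tests it is 1 − P(|Z₁| < 1.96 and |Z₂| < 1.96) under a bivariate normal with assumed correlation r:

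| r | familywise error |
|---|---|
| 0 | 9.75% |
| 0.5 | 9.1% |
| 0.7 | 8.3% |
| 0.9 | 7.0% |
| 0.95 | 6.5% |
| 0.99 | 5.7% |
| 1 | 5.0% |

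**3. Where on that scale the two variables lie.** Write gap = prescribed − effective hours. Then change in gap = change in prescription − change in use. With a fixed prescription the first term is 0, so the change in gap is the change in mean hours with the sign reversed, and the two tests coincide. The more prescriptions change during follow-up, the further apart the two tests can move. The documents do not say which prescription applies, so the position is unknown.

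**4. Weekly SD of hours.** Illustrative seven-night weeks:

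- 0 h every night: mean 0, SD 0
- 4 h every night: mean 4, SD 0
- 8 h every night: mean 8, SD 0
- 0, 0, 4, 8, 8, 0, 4 h: mean 3.4, SD 3.6

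More generally, 6 h on a fraction p of nights gives SD = 6√(p(1 − p)): 0 at p = 0, 3.0 h at p = 0.5, and 0 again at p = 1. The relation to the mean depends on the patients. With p spread uniformly over 0.5 to 1, SD and mean correlate at −0.92. With p symmetric about 0.5, the correlation is 0.

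**5. Baseline hours.** For a new starter, pre-NIV hours are either set to 0, so that change equals the follow-up value, or absent, so that change cannot be computed. For an existing user, change could be computed, but no window is given. Proposed analyses has three repeated measures while four time points (T0 to T3) are scheduled, so it is unclear whether T0 enters the model.

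**The case against.** The strongest reply is that acceptance and adherence are the very indices listed under the latent variable in the Objectives, so Proposed analyses may simply be naming its indicators. Score construction and allocation of α are details that an article leaves to an analysis plan, which is not shown here. That holds for the details. It does not cover the conflict itself: one section fixes a single latent variable and another speaks of primary outcome variables in the plural and by name. An analysis plan can refine a settled primary outcome, but it cannot agree with both statements.

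Several stronger readings are tempting and are not supported:

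- A reader might infer that the two variables are tested separately, each at 5%, with either sufficient. The text does not say so, and a joint test or a requirement that both succeed is not excluded. The error rates above are therefore conditional.
- A reader might multiply two variables by three visits and treat them as six independent tests. Proposed analyses describes an interaction over repeated measures, not visit-by-visit tests.
- A reader might infer near-independent inflation and redundancy together. They cannot both hold: the more the gap duplicates mean hours, the closer familywise error is to 5%.
- A reader might conclude that the SD cannot load on an acceptance factor. It can, as the −0.92 example shows. It measures regularity and may be informative beside the mean. What it lacks is a fixed direction.
- A reader might assume that every patient is new to NIV. The documents neither require this nor exclude existing users.

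Nor is it a fault in itself that the adherence gap moves when the prescription changes; a measure relative to prescription is meant to do so.

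**Conclusion.** The contradiction stands on the wording alone and needs no assumption: one latent variable in the Abstract and Objectives, two named variables with no latent score in Proposed analyses, and a sample size for a single two-group comparison. It must be resolved before unblinded analysis.

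The effect on error control is conditional. It lies between 5% and 9.75% if either variable alone may count as success, and is nil if a joint test or a both-must-succeed rule is intended. The correlations are assumed, and near-redundancy of the two variables would put the figure close to 5%.

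The ambiguous direction of the SD and the unclear baseline do not invalidate the measures. They are good reasons to prefer mean hours at follow-up as the single primary.

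**What to change.** Before unblinded analysis:

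- **Primary:** name one variable, mean ventilator-recorded hours per day over a fixed window before each visit. Count days without use while the patient is alive as 0. Analyse it as a follow-up value without baseline subtraction. State a rule for days after death, since survival is itself a secondary outcome.
- **Test:** state the one between-arm contrast over the visits that decides success. If only post-baseline values are modelled, a treatment-by-time interaction alone would miss a difference that is constant over time.
- **Secondary:** make the adherence gap a secondary outcome, tested only if the primary is significant, and state which prescription it is measured against. Against the prescription at randomisation it would nearly duplicate the primary with the sign reversed, because prescribed hours are balanced between arms in expectation.
- **Supporting:** report the weekly SD descriptively and any latent score as a sensitivity analysis.
- **Alignment:** make the Abstract, Objectives, Sample size and Proposed analyses agree, and say in Sample size which variable and contrast are powered.

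The cost is wording in the protocol and registry. Recruitment is reported as ongoing and no new data are needed. The downside is small: adherence moves from co-primary to gated secondary.

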### Subjects and setting

The study will be conducted in a Clinical and Research Centre, HD Respiratory Rehabilitation Unit, Fondazione Don Carlo Gnocchi, IRCCS Santa Maria Nascente, Milan (Italy), a centre chosen based on documentation of, among other things, patient availability.

We aim to recruit 150 patients with COPD who have been recommended to use NIV based on the GOLD criteria (from moderate to severe) [36, 37].

The *inclusion criteria* are as follows: age 18 years or older; inpatients or outpatients; with moderate (GOLD 2–50% ≤ FEV_1_ < 80% predicted) to severe (GOLD 3–30% ≤ FEV_1_ < 50% predicted) COPD.

The *exclusion criteria* are as follows: refusal of consent; pregnancy; oncological history or history of psychiatric/mental disorders, according to *Diagnostic and Statistical Manual of Mental Disorders, fifth edition* (DSM-V) criteria [38, 39], with the exception of anxiety and depression, as indicated in the patient’s clinical record; immunosuppressive disease as the principal condition; stable use of antidepressant drugs.

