### Sample size

Based on statistical analysis, preventive inherent power and sample size [40] we anticipate that the study will require 150 subjects. We will recruit between 128 subjects (statistical power of 0.80; *α* = 0.05; 1 − *β* = 0.80; *t* (126) =1.97) and 172 subjects (statistical power equal to 0.90; *α* = 0.05; 1 − *β* = 0.90; *t* (170) = 1.97). The inherent power also emphasises that such analyses have been carried out using data for a scientific study that have a comparable primary outcome [33].

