### Recruitment and duration of the study

The study is expected to last 3 years. After the pulmonary clinical visit all patients who meet the inclusion criteria will be asked to join the study. If they agree to do so they will be asked to sign a form to indicate their informed consent to participate. After this they will undergo psychological assessment (baseline, T0). Follow-up assessments will be carried out 3, 6 and 12 months after recruitment (T1, T2 and T3, respectively) using the same procedure.

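### The secondary survival outcome is counted from the start of NIV adaptation, whose timing relative to randomisation is not stated; if any randomised patient starts late or never, the arm comparison departs from intention-to-treat

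*Protocol article*

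**What the plan says.** Under Objectives, the protocol article states: "Survival rates after starting the adaptation to NIV and psychological variables will be considered as secondary outcomes". Under Medical and clinical assessment it lists survival again with the same starting point, to be given in months. No section counts survival from randomisation or recruitment.

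Other statements bear on this:

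- **Proposed analyses:** "The analysis will be performed using the intention-to-treat procedure". No exception is made for survival.
- **Recruitment and duration of the study:** "Follow-up assessments will be carried out 3, 6 and 12 months after recruitment". The scheduled assessments therefore run on a different clock.
- **Subjects and setting:** "We aim to recruit 150 patients with COPD who have been recommended to use NIV". Having started NIV is not an entry condition.
- **Background:** of NIV, "patients often reject it or fail to use it appropriately".
- **Objectives:** the primary objective is to "evaluate the effects of psychological support on the acceptance of, and adherence to, NIV", and a secondary aim is to find predictors of rejection or misuse.

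**The concern.** In a randomised comparison the survival clock should start at randomisation, because that is the moment at which the arms are comparable. Here it starts at an event whose place in the sequence is not given. If that event can fall after randomisation, whether and when it happens is close to what the intervention is meant to change. By the article's own account in the Background, it is also related to prognosis, since rejection or poor use of NIV is said to lead to worse outcomes. A survival comparison that begins there could hide a difference between the arms or create one.

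**Working it through.** **1. The plan's own figures.** The article gives no number for survival. Its sample sizes ("We will recruit between 128 subjects (statistical power of 0.80", and 172 for power 0.90) concern the primary outcome. They reproduce with a two-sample t test at two-sided 5% if a standardised difference of 0.5 is assumed: power is 0.8015 at 128 and 0.9032 at 172. The time origin of survival changes neither figure.

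**2. Order of events.** Let T be time from randomisation to death and D time from randomisation to the start of adaptation.

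- *Start after randomisation (D > 0).* The outcome becomes T − D and exists only for patients with T > D. Deaths before the start drop out. If D differs by arm, the distribution of T − D can differ even when T does not.
- *Never starts.* D does not exist, so the patient has no survival time. An analysis on this clock must omit the patient or invent an origin.
- *Start before randomisation by L months.* Every randomised patient has already survived L months, so the first 12 months after NIV start contain only 12 − L months at risk within the trial. Survival at 12 months is overstated. L is fixed before allocation and has the same distribution in both arms in expectation, so under the null the arm contrast is not biased. All patients can still be analysed as assigned.

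**3. Which order the article supports.** Pointing to a start after randomisation for some patients: entry needs only a recommendation, rejection is expected, and the abstract's Discussion places the intervention within the adaptation process. Pointing the other way: the primary outcome is a change from baseline in ventilator-recorded hours, which could mean that some or all patients already have ventilator data at T0. The text does not settle it. Figures 1 and 2, which might, were not available for this check.

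**4. Illustration of size. All rates are assumed; none is in the article.** Take 75 per arm (150/2, assuming equal arms) and no true survival effect. A share a of patients always starts, a share s starts only with support, and the rest, 1 − a − s, never start. Their 12-month mortalities are m1, m2 and m3.

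- All randomised, either arm: a·m1 + s·m2 + (1 − a − s)·m3, so the difference is 0.
- Starters, support arm: (a·m1 + s·m2)/(a + s). Starters, control arm: m1.
- Patients with no time zero: 75(1 − a − s) + 75(1 − a).

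| Start, support vs control | No time zero, of 150 | m1 / m2 / m3 | All randomised, both arms | Starters, support | Starters, control | Spurious difference (points) |
|---|---|---|---|---|---|---|
| 95% vs 90% | 3.75 + 7.5 = 11.25 | 10 / 15 / 20% | 10.75% | 10.26% | 10% | 0.26 |
| 95% vs 90% | 11.25 | 10 / 20 / 30% | 11.50% | 10.53% | 10% | 0.53 |
| 90% vs 80% | 7.5 + 15 = 22.5 | 10 / 15 / 20% | 11.50% | 10.56% | 10% | 0.56 |
| 90% vs 80% | 22.5 | 10 / 20 / 30% | 13.00% | 11.11% | 10% | 1.11 |
| 90% vs 70% | 7.5 + 22.5 = 30 | 10 / 15 / 20% | 12.00% | 11.11% | 10% | 1.11 |
| 90% vs 70% | 30 | 10 / 20 / 30% | 14.00% | 12.22% | 10% | 2.22 |

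Last row: (0.70 × 0.10 + 0.20 × 0.20)/0.90 = 0.11/0.90 = 0.1222. The excess falls on the support arm because support brings in patients with a worse prognosis.

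The bias can also conceal a benefit. Assume that 20% of controls and 10% of supported patients never start, and that starting itself brings mortality from 40% to 15%. All randomised: control 0.8 × 0.15 + 0.2 × 0.40 = 20.0%, support 0.9 × 0.15 + 0.1 × 0.40 = 17.5%, a 2.5-point benefit. Starters only: 15% against 15%.

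**The case against.** The case against has force on several points.

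- **Starting adaptation is not the same as accepting NIV.** Adaptation is a process; a patient can begin it and then reject the device, and that patient does have a time zero. No sentence says that any randomised patient never begins. A reader might infer that refusers certainly lack an origin, but the article supports only that this is possible. This point stands, so the claim is conditional.
- **A reader might infer that intention-to-treat is breached whichever way the events fall.** It is not. If adaptation precedes randomisation, the lead time is balanced between arms in expectation and nobody is excluded. Only absolute survival is distorted.
- **No survival comparison between arms is spelled out, and nothing restricts survival to starters.** This is true: Proposed analyses describes the treatment-by-time test for the primary outcomes only. But survival is a named secondary outcome of a two-arm trial, intention-to-treat is stated without exception, and the origin as written cannot be applied to a patient who has not started.
- **The size is assumed and small for a trial of this size.** This stands. Even the 2.5-point difference above has a standard error of √(0.20 × 0.80/75 + 0.175 × 0.825/75) = 0.064, or 6.4 points, and power of about 7%.
- **The choice of survival method may be left to the full protocol or analysis plan.** Agreed, and its absence is no part of this point. The origin is different, because the article fixes it, twice.

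**Conclusion.** The point holds in conditional form. The article fixes an origin for survival that is not randomisation and does not say how the two relate. If some randomised patients start adaptation later or never, the comparison is conditioned on an event that the intervention may affect, earlier deaths are lost, and the result is not intention-to-treat. If all start beforehand, the arm contrast is sound in expectation under the null and only absolute survival is too favourable.

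The article gives neither start rates nor mortality, so the size of any bias cannot be derived from it. The 0.3 to 2.2 points above rest wholly on assumed rates, and the true bias may be small. Survival is one secondary outcome; the primary outcome and the sample size are untouched. The change is still worth making, because counting from randomisation is right whatever the order of events.

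**What to change.** In Objectives and in Medical and clinical assessment, define survival from the date of randomisation for all randomised patients, analysed in the arm to which they were assigned. Report survival from the start of NIV adaptation only as a description of those who start, not as a comparison of randomised arms. It would also help to add a sentence stating when adaptation begins relative to randomisation.

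The cost is a wording change in two places. Allocation runs through a centralised service, which should supply the randomisation date. The one practical demand is that vital status be sought also for patients who do not start NIV. The article does not say that it is already held for everyone, and patients who withdraw consent to follow-up may remain unknown.
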